#### Modifications

We do not offer a cross-over treatment in this study as the episodes of vertigo are fluctuating in nature with a potential difference in “baseline” characteristics before and after cross-over treatment which makes it difficult to compare. Furthermore, it is not possible to modify a ventilation tube insertion if the participant is unsatisfied with the treatment, in response to harms, or as a participant request. Therefore, if the participant is unsatisfied with the current treatment, then he/she has the right to drop out of the study.

#### Adherence

The participant will be followed once every month for the first 3 months to improve the adherence to the intervention and to perform tympanometry to detect if spontaneous extrusion of the ventilation tube has occurred.

#### Concomitant care

Any medication for Meniere disease that a patient takes at inclusion is continued with unchanged doses during the study period. Medications, such as anti-histamine suppositories, to alleviate acute vertigo attacks are permitted. The use of such rescue medications is recorded by the patient.

Other relevant treatment options for patients suffering from Menière’s disease (i.e. Meniett-treatment, intratympanic steroid injection, or surgery) are not allowed during the trial.

### Outcomes

#### Primary outcome (main study 3 months)

The number of spontaneous vertigo attacks lasting more than 20 min during the study period will be compared between the two study groups.

This outcome was chosen as vertigo is the most disabling symptom of Menière’s disease.

#### Secondary outcomes (main study 3 months)

The secondary outcomes of this study are comparisons between the two study groups regarding:Pure-tone audiometry of affected ear, four-tone average of 500, 1000, 2000, and 3000 Hz (dB)Pure-tone audiometry of affected ear, three-tone average of 125, 250, and 500 Hz (dB)Speech audiometry of affected ear, discrimination (%)AAO-HNS Functional level scale (1–6)Subjective hearing (0–10 arbitrary scale)The subjective intensity of ear fullness/pressure (0–10 arbitrary scale)The subjective intensity of dizziness/unsteadiness (0–10 arbitrary scale)The subjective intensity of tinnitus (0–10 arbitrary scale)Need of “escape medication”Number of subjects leaving the study because of treatment failureNumber of subjects satisfied with the treatmentSerious adverse events (as defined by the ICH-GCP)

These outcomes were chosen to assess any possible effects of treatment on hearing, functional level, and subjective symptoms.

The number of vertigo attacks, need for escape medication, and level of subjective symptoms will be recorded weekly by the study subject on a standardized form. Hearing tests will be performed at inclusion and after 3 months. A tympanometry will be performed after 1, 2, and 3 months. Assessment of AAO-HNS functional level scale will be made at inclusion and after 3 months. Menière’s disease staging (I–IV) will be decided at inclusion. Four-tone average of worst audiogram during the last 6 months: < 26 dB = Stage 1, 26–40 dB = Stage 2, 41–70 dB = Stage 3, > 70 dB = Stage 4. The equipment for hearing tests is maintained and calibrated by each study centre.

#### Primary outcome (the extended study of up to 24 months)

Time to treatment-failure will be compared between the two study groups and presented as a Kaplan-Meier plot.

### Participant timeline

The participants will be followed for 3 months after the start of treatment with follow-up visits at (Table 1):One month ± 4 daysTwo months ± 4 daysThree months ± 4 days

**Table 1 Tab1:** Participant timeline

	Study period							
	Enrolment	Allocation	Post-allocation					Close-out
Timepoint	-t_1_	0	t_1_	t_2_	t_3_	t_4_	t_5_	t_x_
**Enrolment**								
Eligibility screen	X							
Informed consent	X							
Allocation		X						
**Interventions**								
Ventilation tube insertion		X						
Sham-treatment		X						
**Assessments**								
Subjective symptom score-scheme^a^		X	X	X	X			
AAO-HNS functional level scale		X			X	X	X	
Pure-tone and speech audiometry		X			X			

**Timeline:**

t_1_: At one month

t_2_: At two months

t_3_: At three months

t_4_: At three to six months from t_3_

t_5_: At three to six months from t_4_

t_6_: At three to six months from t_5_

t_7_: At three to six months from t_6_

t_8_: At three to six months from t_7_

t_9_: At three to six months from t_8_

^a^Patients will be asked to fulfill a weekly subjective symptom score-scheme regarding dizziness, tinnitus, hearing and aural fullness.

The participants will then be asked if they want to participate in a follow-up study which entails a follow-up every 3 to 6 months for a maximum of 24 months.

**Table Taba:** 

4 mandatory visits:	Inclusion, month 1, month 2, month 3			
**Visit**	**Inclusion**	**Month 1**	**Month 2**	**Month 3**
Inclusion assessment	**X**			
Informed consent	**X**			
AAO-HNS Function Level Scale	**X**			**X**
Tympanometry	**X**	**X**	**X**	**X**
Pure tone audiometry	**X**			**X**
Speech audiometry	**X**			**X**
Weekly subj. symptom form	X	**X**	**X**	**X**
Placement of tube or sham	**X**			

### Sample size

The primary outcome in the study will be the number of attacks within the first 3 months after ventilation tube insertion. Because this is count data (i.e. an incidence rate) a Poisson distribution is expected, and a Poisson regression model most likely will give the best fit for analysis of the primary outcome.

The simulation software ”Powersim” developed for the used statistical package, STATA, was applied for Power calculations.

Given the lack of published data concerning the expected effect of ventilation tube insertion, we chose to assume a 50% reduction in the intervention group, which we believe is realistic as well as a necessity. A 50% reduction gives an Incidence Rate Ratio (IRR) of 0.5 and an ln(IRR) of −0.69315.

Using an alpha value of 0.05 and an expected effect size of 0.5 (ln(0.5) = −0.69315), and to obtain a power of 0.8, an expected 94 participants in total or 47 participants in each group will be necessary. To adjust for drop-outs, a safety margin of 10% results in 104 participants in total.

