#### Inclusion criteria

Participants aged 18 years or older with definite or probable unilateral Menière’s disease according to the diagnostic criteria formulated by the Classification Committee of the Bárány Society, The Japan Society for Equilibrium Research, the European Academy of Otology and Neurotology (EAONO), the Equilibrium Committee of the American Academy of Otolaryngology – Head, and Neck Surgery (AAO-HNS), and the Korean Balance Society [16]:A.Two or more spontaneous episodes of vertigo, each lasting 20 min to 12 hB.Audiometrically documented low- to medium-frequency sensorineural hearing loss in the affected ear on at least one occasion before, during, or after one of the episodes of vertigoC.Fluctuating aural symptoms (hearing, tinnitus, or fullness) in the affected earD.Not better accounted for by another vestibular diagnosis

Furthermore, the patient must have experienced at least two vertigo attacks during the last 3 months before inclusion.

In probable Menière’s disease, the diagnostic criteria cover the same points (A, C, D). However, episodes of vertigo or dizziness may last from 20 min to 24 h [17]. Furthermore, the patients must have experienced at least two spontaneous vertigo attacks lasting more than 20 min during the past 3 months [16].

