### Statistics

The intervention group and the control group will be compared concerning all outcomes based on the intention-to-treat principle. That is, all participants will be analysed in the groups to which they were randomized, regardless of whether they adhered to the allocated intervention.

In general, count data will be analysed using Poisson regression, continuous data with mixed linear modelling, and binary data with logistic regression. For the speech audiometry, we plan to dichotomize the data into an ≥8% decrease or not, to be able to apply logistic regression. For the AAO-HNS Functional Level Scale, we plan to dichotomize the outcome into a change ≥2 or not, for the same purpose.

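### The primary attack count is planned and tested with plain Poisson regression, with no provision for overdispersion and no stated sham rate behind the 80% power

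*Protocol article*

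**What the plan says.** The primary outcome of the main study is "the number of attacks within the first 3 months after ventilation tube insertion" (Protocol article, Sample size). The same section gives the reason for the model: "Because this is count data (i.e. an incidence rate) a Poisson distribution is expected", and it continues that "a Poisson regression model most likely will give the best fit for analysis of the primary outcome". The Statistics section states "In general, count data will be analysed using Poisson regression", and the outcome tables below it list Poisson regression for the primary outcome and for the need for escape medication.

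The article mentions no robust variance, scale factor or negative binomial alternative. For the functional level scale, by contrast, the table does name a fallback (a bootstrapped linear regression).

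The planning inputs are alpha 0.05, power 0.8 and an incidence rate ratio (IRR) of 0.5, run in simulation software whose settings are not given. The result is that "an expected 94 participants in total or 47 participants in each group will be necessary", raised to 104 by a 10% margin. No attack rate for the sham arm is stated. The nearest figure is the entry rule that "the patient must have experienced at least two vertigo attacks during the last 3 months before inclusion".

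**The concern.** A two-arm Poisson model treats every patient in an arm as having the same underlying attack rate, with attacks occurring independently. The eligibility and care rules make that unlikely: entry has a floor of two attacks but no ceiling, definite and probable disease are both admitted, and each patient's existing Menière medication continues. Differences in rate between patients push the variance above the mean, and the model-based standard error ignores the excess.

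The superiority claim rests on this intention-to-treat comparison, and the planned interim analysis uses the same endpoint. If the standard error is too small, an inert tube would be declared effective more often than the nominal 5%, and the confidence interval for the IRR would be too narrow. The sample size makes the same assumption, so the 80% power describes the design only if there is no overdispersion and the sham rate is whatever value was entered.

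**Working it through.** **Inputs.** From the Sample size section: IRR 0.5 (ln = −0.69315), alpha 0.05, power 0.8, 47 per arm. From Sequence generation: 1:1 allocation. Assumed because not stated: a two-sided test, the sham mean μ (attacks in 3 months), and the dispersion k, with variance = μ + kμ² and so variance/mean φ = 1 + kμ.

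**1. Reproducing 47 per arm.** The required variance of ln(IRR) is (0.69315 / (1.960 + 0.842))² = 0.0612. Under Poisson the variance is (1/μ + 1/(0.5μ))/n = 3/(nμ). Setting n = 47 gives μ = 3/(47 × 0.0612) = 1.04. Three other standard formulas give 0.96, 0.97 and 1.00, and simulating the Poisson Wald test at μ = 1.0 gives 80.3% power. One-sided, the implied rate would be 0.76 to 0.82. So 47 per arm corresponds to about 1 sham attack in 3 months, half the entry minimum. At μ = 2 the Poisson formula needs only 25 per arm. The margin is in order: 94 × 1.10 = 103.4, rounded up to 104.

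**2. Type I error of the plain Poisson test.** If the true variance is φ times the mean, the test statistic is too large by √φ. The actual two-sided error is 2 × (1 − Φ(1.96/√φ)). The simulations use negative binomial counts with 47 per arm and no treatment effect.

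| φ (assumed) | Formula | Simulated, for example |
|---|---|---|
| 1.25 | 8% | 7.6% (μ=1, k=0.25) |
| 1.5 | 11% | 10.8% (μ=1, k=0.5) |
| 2 | 17% | 16.1% (μ=1, k=1) |
| 3 | 26% | 25.5% (μ=2, k=1) |
| 5 | 38% | 38.2% (μ=4, k=1) |

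With sandwich variance on the same Poisson model, simulated error is about 5.5 to 7% across the settings tried (μ 1 to 8, k 0.25 to 2).

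**3. Power when the extra variance is allowed for.** Under a negative binomial model the variance of ln(IRR) is (3/μ + 2k)/n. For μ = 2, k = 1 and n = 47 this is 3.5/47 = 0.0745, with standard error 0.273. Then 0.693/0.273 − 1.96 = 0.58, and power is 72%. Power with 47 per arm, with the number per arm needed for 80% in brackets:

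| Sham mean μ | k = 0.5 | k = 1 | k = 2 |
|---|---|---|---|
| 1 | 66% (66) | 57% (82) | 43% (115) |
| 2 | 85% (41) | 72% (58) | 53% (90) |
| 4 | 95% (29) | 82% (45) | 59% (78) |

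Every μ and k in this table is an assumption. Power of 80% with 47 per arm requires 3/μ + 2k = 47 × 0.0612 = 2.88, that is k = 0.69 at μ = 2 or k = 1.06 at μ = 4.

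**The case against.** The strongest reply is that the variance estimator is analysis-plan detail. The plan is not shown, the article condenses a longer protocol, and the wording is hedged. Poisson regression with robust variance is still Poisson regression. Part of this stands: an unseen document may already contain the remedy. But the article does more than stay silent. It derives a Poisson distribution from the mere fact of counting, builds the sample size on that, and names the model again in the Statistics section and the outcome table. The hedged wording names no alternative.

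It can also be said that the protocol contains no evidence of overdispersion. The remark that "the episodes of vertigo are fluctuating in nature" explains why cross-over was rejected. It concerns change within a patient over time, not spread between patients. That is fair, and the point here does not rest on it. The eligibility and care rules make differing rates likely, but they do not measure them.

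Three stronger readings are tempting and not supported:

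- A reader might infer a false-positive rate of 16 to 59%. The 59% end needs a variance about 13 times the mean (for example μ = 6, k = 2), and the 16% end already assumes a ratio near 2. At μ = 1 with k of 0.25 to 0.5 the error is 8 to 11%. The documents give no dispersion figure from which to choose.
- A reader might call a sham rate near 1 implausible, since entry requires two attacks. The Abstract, however, expects frequent spontaneous relief and a large placebo response, so a fall to about 1 is possible. The rate is unstated and unjustified, not shown to be wrong.
- A reader might conclude that 94 patients are too few. Under pure Poisson a higher sham rate makes 94 more than enough, and with overdispersion the answer depends on μ and k.

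**Conclusion.** The concern holds for how the variance is handled. The protocol names plain Poisson regression for its primary test and supports it with an argument that does not follow. Even modest overdispersion lifts the error above nominal, to about 11% at a variance/mean ratio of 1.5 and 17% at 2. These figures rest on assumed ratios and a two-sided test, and the formula and simulation agree closely.

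On sample size the conclusion is narrower. The stated power cannot be checked from the stated inputs, and it is conditional on an undisclosed sham rate and on variance equal to the mean. Whether the trial is under-powered cannot be settled from the protocol.

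**What to change.** Before unblinding:

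- Prespecify one primary analysis of the attack count: negative binomial regression (log link, log observation time as offset) or Poisson regression with sandwich variance. Name which is primary. The effect measure stays an IRR. The sandwich version runs slightly above nominal at this sample size (about 5.5 to 7%), which should be acknowledged if it is chosen.
- Apply the same choice to the escape-medication count.
- Restate the Sample size paragraph with the assumed sham mean and dispersion, their justification and the sidedness of the test, and show the power of 47 per arm over a range of both.

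The cost is wording in the Sample size and Statistics sections and a rerun of the power simulation. No extra patients are proposed. The downside is wider confidence intervals and possibly a less favourable stated power. Choosing the variance method after the results are known would be open to the charge of being data-driven.

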### Recruitment

We have been in contact with DØNHOF (the danish ear, nose, throat-specialists organization), and DØNHOF is willingly conveying this contact by sending e-mails as well as bringing information about the project on their web page (http://www.doenho.dk). Besides, we will present the project at relevant conferences such as DSOHH (the Danish Organization of Ear, Nose, Throat, and Head Neck Surgery) as well as DSFV (the Danish Organization of Vestibulogy). At this point, we have received permission from the Committee on Health Research Ethics to perform the trial. Therefore, we are about to initiate contact with the ENT specialists. Hence, we do not know the exact locations and responsible ENT specialists yet. As soon as it is clarified which clinics will be participating in the study, it will be announced by an additional protocol for the Committee on Health Research Ethics.

Participants will be enrolled in cooperation with private-practising ENT specialists in Denmark and Sweden. The ENT specialists will be given a scheme on inclusion criteria to include relevant participants. An estimated 104 participants are needed in cooperation with an estimated 40 ENT specialists. We expect each ENT clinic to enrol 2.5 participants per year on average.

## Methods: assignment of interventions

### Allocation

#### Sequence generation

Once informed consent has been obtained, the participant will be randomly assigned to either a sham or experimental group with a 1:1 allocation without site-stratification as per a computer-generated randomization schedule. An independent statistician will generate the allocation sequence.

#### Concealment mechanism

Participants will be randomized using REDCap, a web-based randomization service. The allocation concealment will be ensured, as the service will not release the randomization code until the patient has been recruited into the trial, which takes place after all baseline measurements have been completed in the RedCap system.

#### Implementation

The statistician will generate the allocation sequence. The ENT specialists will screen and obtain informed consent. The ENT specialist will be given a direct phone number to a project nurse who will perform the registration and randomization of the participant.

### Blinding

#### Masking

Participants, care providers, data collectors, outcome assessors, research personnel, and data analysts will be blinded to treatment allocation. However, the ENT specialist performing the insertion of the ventilation tube or sham treatment will inevitably be aware of treatment allocation.

At the end of the final visit, the participants will be asked what treatment they believe to have received. This will enable an assessment of the adequacy of blinding.

#### Emergency unblinding

The treatment allocation of a participant may be unblinded in case of an emergency where the treating physician is unable to adequately treat the participant without being aware of treatment allocation. The investigator will be notified, and the investigator will contact the data-management team for unblinding. The reason for unblinding will be documented.

### Data collection plan

Pure-tone audiometry, speech audiometry, and assessment of AAO-HNS (the Committee on Hearing and Equilibrium of the American Academy of Otolaryngology – Head and Neck Surgery) functional level are performed when a participant enters the study and is repeated after 3 months of treatment. Following inclusion, a weekly questionnaire on symptoms will be filled out by the participants.

#### Audiometric tests

The audiometric tests include pure-tone audiometry: an average of 500, 1000, 2000, and 3000 Hz and an average of 125, 250, and 500 Hz (dB), speech audiometry: single-syllable phonetically balanced word lists, speech discrimination (%), and tympanometry (to indicate function and patency of active tubes). The audiometric tests will be performed at inclusion and after 3 months. A tympanometry will be performed after 1, 2, and 3 months to objectively assess tube patency.

#### Functional level scale

The AAO-HNS functional level scale (see Additional file 1: Appendix 5.1) consists of written descriptions of how Menière’s disease affects the life of the participants, from no impact at all (level 1) to handicapped and unable to work (level 6). The participant chooses the description that fits best. The form will be filled out at inclusion and after 3, 6, 12, 18, and 24 months.

#### Self-evaluation of symptoms

Once every week the study subject fills out a form for self-evaluation of symptoms (see Additional file 1: Appendix 5.2). The form includes the number and duration of vertigo attacks longer than 20 min, need and type and dose of escape medication for vertigo, the subjective intensity of dizziness/unsteadiness (VAS scale), subjective hearing loss (VAS scale), the subjective intensity of ear fullness/pressure (VAS scale), and subjective intensity of tinnitus (VAS scale).

All procedures are clinical routine procedures carried out every day at every ENT clinic in Denmark and Sweden, except the assessment of the functional level and filling out forms for self-evaluation of symptoms.

#### Retention

We will try to promote participant retention by following the participant once every month for the first 3 months, then every third month until the end of the trial. We will send e-mails to participants before data collection to remind them of the upcoming data collection. If a participant is discontinued from the trial or withdraws consent and the dropout is before the end of the first 3 months, then the patient will be asked to fill out a functional level scale. If the dropout is after the first 3 months, we will ask the participant if we may continue to record data relevant to the trial.

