#### Analysis population and missing data

We plan to test superiority using the intention-to-treat set, considering all patients as randomized regardless of whether they received the randomized treatment. We propose declaring surgical management superior to sham treatment, only if shown to be superior using the intention to treat analysis set. Further analysis can be done using per-protocol analysis.

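### Participants who leave before month 3 are not asked to go on recording attacks, so the primary count stops early, probably most often in those doing worst

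*Protocol article*

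**What the plan says.** **Outcome and source.** The section on the main study's primary outcome states: "The number of spontaneous vertigo attacks lasting more than 20 min during the study period will be compared between the two study groups". The Secondary outcomes section adds how attacks are captured: "The number of vertigo attacks, need for escape medication, and level of subjective symptoms will be recorded weekly by the study subject". The Self-evaluation of symptoms section describes the same weekly form.

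**Data after exit.** The Retention section covers participants who are discontinued and those who withdraw consent in one rule, split by time. For early exit: "the dropout is before the end of the first 3 months, then the patient will be asked to fill out a functional level scale". For late exit: "If the dropout is after the first 3 months, we will ask the participant if we may continue to record data relevant to the trial".

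**Routes out.** The Modifications section states that "if the participant is unsatisfied with the current treatment, then he/she has the right to drop out of the study". Concomitant care rules out Meniett treatment, intratympanic steroid and surgery during the trial. The number leaving because of treatment failure is a listed 3-month secondary outcome.

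**Analysis.** The Statistics section promises that "all participants will be analysed in the groups to which they were randomized, regardless of whether they adhered to the allocated intervention". Analysis population and missing data rests the superiority decision on this set, "considering all patients as randomized regardless of whether they received the randomized treatment".

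**The concern.** The two Retention rules sit the wrong way round for the primary outcome. Before month 3, when attacks are still being counted, a leaver is asked for a 1-to-6 scale of how the disease affects daily life. After month 3, when the count is complete, a leaver is asked whether recording may continue.

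The weeks lost this way are unlikely to be a random sample. A participant with frequent attacks has reason to be dissatisfied, cannot have the main alternative treatments inside the trial, and is offered departure as the remedy. If the tube reduces attacks, more such participants will be in the sham arm. Their uncounted attacks would have widened the difference between the arms.

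The trial is sized for 80% power at a rate ratio of 0.5, with a 10% margin for drop-outs. That margin replaces lost numbers. It does not protect against selective loss of the highest counts. Nor can a later analysis plan recover counts that nobody asked for.

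**Working it through.** **1. The plan's own figure.** Sample size section: 94 participants plus 10% gives 94 × 1.1 = 103.4, rounded up to 104, as stated. Dividing instead, 94 / 0.9 = 104.4, gives 105. The 94 cannot be re-derived because no control attack rate or dispersion is given. The attack and exit rates below are therefore assumptions.

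**2. A check by hand.** Assume:
- underlying attack rates vary between patients with gamma dispersion 1 (an exponential distribution);
- the fraction f with the highest rates leaves at week 6 of 12.

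For an exponential distribution, the top fraction f carries a share S = f(1 − ln f) of all attacks:
- f = 0.05: S = 0.05 × (1 + 2.996) = 0.200
- f = 0.10: S = 0.10 × (1 + 2.303) = 0.330
- f = 0.20: S = 0.20 × (1 + 1.609) = 0.522

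Relative to full follow-up, each arm's mean is multiplied by:
- raw count cut at exit: 1 − S/2
- count per week observed: (1 − S/2) / (1 − f/2)
- completers only: (1 − S) / (1 − f)

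With 10% of sham and 5% of tube patients leaving, the rate ratio is multiplied by:
- raw: 0.900 / 0.835 = 1.078, so 0.50 becomes 0.54
- with offset: (0.900 / 0.975) / (0.835 / 0.95) = 1.050, so 0.50 becomes 0.53
- completers: (0.800 / 0.95) / (0.670 / 0.90) = 1.132, so 0.50 becomes 0.57

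Simulation with 52 per arm, where leavers are whole patients, gives 0.53, 0.52 and about 0.55. With 20% sham and 5% tube leaving, the same formulas give multipliers of 1.218, 1.124 and 1.409, so 0.50 becomes 0.61, 0.56 and 0.70 (simulation: 0.60, 0.56 and 0.68). With equal fractions leaving, every multiplier is 1. Swapping the arms (5% sham, 20% tube) inverts them, and 0.50 becomes 0.41, 0.44 and 0.35 (simulation: 0.42, 0.45 and 0.37).

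**3. Exit triggered by attacks, same rule in both arms.** Simulated over 12 weeks. Control mean 2, 4 or 6 attacks; dispersion 0 (Poisson) or 1 (gamma-Poisson). From week 4, a patient with at least 2 (or 3) attacks in the last 4 weeks leaves with a weekly probability of 5% or 10% (or 30%). Selected results for a true ratio of 0.50:

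| Control mean | Dispersion | Trigger, weekly probability | Left, sham / tube | Raw | Offset | Completers |
|---|---|---|---|---|---|---|
| 2 | 0 | 3, 30% | 5.8% / 0.9% | 0.51 | 0.50 | 0.53 |
| 2 | 1 | 2, 10% | 10.7% / 4.3% | 0.53 | 0.51 | 0.55 |
| 2 | 1 | 3, 30% | 10.1% / 2.8% | 0.55 | 0.53 | 0.60 |
| 4 | 1 | 3, 30% | 25.2% / 10.0% | 0.58 | 0.54 | 0.66 |
| 6 | 0 | 2, 10% | 37.5% / 18.0% | 0.55 | 0.50 | 0.49 |
| 6 | 1 | 3, 30% | 36.5% / 17.9% | 0.60 | 0.54 | 0.69 |

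Over all settings: raw 0.51 to 0.60, offset 0.50 to 0.54, completers 0.49 to 0.69. Full follow-up returns 0.50. With a true ratio of 1.0, all three analyses stay at about 1.0.

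**The case against.** **Only a functional scale?** The Retention section does not say that weekly forms stop, and a journal article condenses the full protocol. That is fair. But the next sentence does request continued recording, and confines it to later leavers, so the inference is reasonable. Forms returned before exit also remain usable: the count is truncated, not lost.

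**Consent.** A participant who withdraws consent to data collection may rightly be followed no further. This stands. The fault is that the rule treats being discontinued and withdrawing consent alike.

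**Contradiction of intention-to-treat.** A reader might infer one. The protocol defines the principle as analysing participants in their randomized groups whatever their adherence, and incomplete outcome collection does not breach that wording. It weakens the comparison.

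**False signals when the tube does nothing.** A reader might infer these from the 20% versus 5% scenario, whose multipliers turn a true 1.0 into 1.22 (raw), 1.12 (offset) or 1.41 (completers). But that scenario assumes a fourfold gap in exit of the worst-affected although attack rates are equal. With blinded participants and a sham that imitates the procedure, the documents give no reason to expect it. Unequal exit for other reasons, such as unblinding or tube complications, could bias either way; this is a possibility, not a finding.

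**Missing offset or imputation rule.** These are commonly left to an analysis plan, which is not shown. The Sample size section already speaks of an incidence rate and a rate ratio, which fits a person-time model. Neither is raised as a fault.

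**Conclusion.** The point holds as a defect in the data-collection rule. Followed as written, the rule leaves the primary outcome unpursued after early exit, and the routes out that the protocol itself names make those leavers likely to have high attack rates.

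The probable consequence is dilution of a real effect. A true 0.50 moves to about 0.50 to 0.60 with truncated counts and about 0.49 to 0.69 in completers. At exit close to the plan's 10% margin the shift is modest: roughly 0.51 to 0.55 with truncated counts and 0.55 to 0.60 in completers. The upper ends need a quarter or more of the sham arm to leave. All of this rests on assumed attack rates, dispersion and exit behaviour. The direction is better supported than the size.

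Severity: should be fixed. The likely bias is conservative and may be small, but the repair is cheap and cannot be made at analysis.

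**What to change.** In the Retention section:

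- Distinguish leaving treatment or visits from withdrawing consent to data collection.
- Ask every participant who leaves before month 3, and does not refuse, to keep completing the weekly attack form to month 3. The functional level scale can be requested as well.
- State that these counts enter the primary intention-to-treat analysis, so that Retention agrees with the Statistics section and with Analysis population and missing data.

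The patient information needs a matching sentence. The cost is a few extra reminder contacts for a form already in use. Enrolment began in October 2021, so the change would apply to participants still inside their first 3 months and to those yet to enrol. Some leavers will refuse, so the loss will shrink but not vanish.
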